### 3.7 Timing of Outcome Assessment

The last patient visit was on 11 December 2017. The mailing of the follow-up questionnaires will be on 7 May 2018. For further details, see Study Protocol, Section 9, Study Procedures, pp. 30ff.

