#### 6.6.5 Pain Intensity, Follow-Up

For research question 1b, the follow-up measurement of pain (outcome variable `nrs_fu_1`) will be analysed as well, using the same method as described in Section 6.2.2. For the imputation of missing values, the following predictor variables will be used:

- pain intensity measured at follow-up (`nrs_fu_1`)
- effectiveness briefing group (EXPBRIEF)
- side effects briefing group (SIDEBRIEF)
- pain intensity at first visit (`screeningb_1a_4a`)
- pain intensity after acupuncture treatment (`nrs_8_1`)
- baseline optimism (`LOT_BL_optim`)
- baseline pessimism (`LOT_BL_pessim`)
- acupuncture therapist (`acupuncturist`)
- gender (`pers_1_2`)
- age (`age`)
- duration of pain at first visit (`painduration`)
- pain bothersomeness at baseline (`nrs_1a_2`)
- pain bothersomeness at the end of acupuncture treatment (`nrs_8_2`)
- depression (`PROMIS_BL_depression.theta`)
- CARE score (`CARE_1a_red1`)

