| Study Schedule:                        | 
FPFV March 2016
LPLV December 2017
                                                                                                                                                                                                                                                                                                                                                                                                                                                                                                                                                                                                                                                                                                                                                                                                                                                                                                                                                                                                                                                                                                                                      |

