### **9.3.8 Follow up (Visit 9)**

Six months after the last visit, patients will again be contacted and asked to fill out the follow up questionnaire (P12) including NRS (P7) and PROMIS (P3). They will receive the questionnaire by mail and will be asked to send it back to the study office in the prepaid questionnaire.

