## **11.3 Planned Analyses**

### **11.3.1 Datasets to be Analyzed, Analysis Populations**

The analyses will be tested for the intention to treat population using all available data.

Group allocations (briefing interventions):

- High expectancy vs. regular briefing
- Intense side effects briefing vs. regular side effects briefing

Measurement time points (data acquisition during the experiment):

- Baseline
- After 2 weeks
- After 4 weeks
- 6-months follow-up
- Study end

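### SAP 3.7's single follow-up mailing date conflicts with the protocol's six months after each patient's last visit, and the follow-up models have no term for elapsed time

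*Combined protocol and SAP*

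**What the plan says.** Protocol 9.3.8 ties follow-up to the patient's own course: "Six months after the last visit, patients will again be contacted and asked to fill out the follow up questionnaire". The study schedule places this visit at month 6, and Protocol 11.3.1 lists the time point as "6-months follow-up".

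SAP 3.7 states "The last patient visit was on 11 December 2017" and then "The mailing of the follow-up questionnaires will be on 7 May 2018". It gives no other mailing date and closes with a pointer: "For further details, see Study Protocol, Section 9, Study Procedures, pp. 30ff". It does not say whether 7 May 2018 applies to every patient or only to the last ones.

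For the start of the trial the only figure is the planned one in the protocol synopsis, "FPFV March 2016".

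SAP 6.6.5 analyses follow-up pain (`nrs_fu_1`) "using the same method as described in Section 6.2.2", that is, with the end-of-treatment ANCOVA. SAP A.3 and A.4 do the corresponding for the PROMIS scores and bothersomeness. None of these models contains time since treatment, and neither does the imputation list in 6.6.5. The SAP gives no visit window and no sensitivity analysis for timing. The glossary labels the time point simply as follow-up.

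**The concern.** A rule that counts from each patient's last visit gives a common interval and many mailing dates. A single mailing date gives the reverse: one date and as many intervals as there are treatment end dates. In a trial that recruited over many months, the two cannot both hold for all patients.

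The stake is what the follow-up estimate means. If the intervals vary widely, the briefing coefficient averages over an unstated range of elapsed times and cannot be offered as the six-month effect the protocol promised. If the briefing effect fades, that average would lie below the effect at six months; the documents give no figure on fading. Any change in pain or PROMIS with elapsed time also goes into the residual and costs precision. The SAP treats elapsed time as relevant elsewhere: the side-effects model in 6.2.3 includes days since the first session, derived from recorded session dates.

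**Working it through.** Inputs:

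- Last patient visit: 11 December 2017 (SAP 3.7), taken as the end of that patient's treatment.
- Mailing date: 7 May 2018 (SAP 3.7).
- Follow-up rule: six months after the last visit (Protocol 9.3.8).
- First visit: March 2016, planned (protocol synopsis). No actual date is given.
- Treatment: 4 weeks, taken as 28 days (protocol synopsis).
- One month = 365.25 / 12 = 30.44 days.

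**Last patient, needed on either reading.** 11 December 2017 to 7 May 2018 is 20 + 31 + 28 + 31 + 30 + 7 = 147 days, and 147 / 30.44 = 4.8 months. Six months after 11 December 2017 is 11 June 2018, which is 24 + 11 = 35 days after the mailing date. The protocol's six months is therefore not reproduced for this patient.

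**First patient, if 7 May 2018 applies to everyone.** Interval = mailing date − (first visit + 28 days).

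| First visit | End of treatment | Days to 7 May 2018 | Months |
|---|---|---|---|
| 1 March 2016 (planned month, earliest) | 29 March 2016 | 769 | 25.3 |
| 31 March 2016 (planned month, latest) | 28 April 2016 | 739 | 24.3 |
| 1 June 2016 (assumption) | 29 June 2016 | 677 | 22.2 |
| 1 September 2016 (assumption) | 29 September 2016 | 585 | 19.2 |

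The literal reading thus runs from 4.8 months to about 24 to 25 months on the planned start, or to about 19 months if the first visit was as late as September 2016.

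**Share near six months on the literal reading.** This assumes treatment ends spread evenly from the planned start to 11 December 2017. A mailing 5 to 7 months after treatment corresponds to treatment ends from 6 October to 6 December 2017, which is 61 days. The whole span is 592 to 622 days, so the share is 61 / 622 to 61 / 592, or about 10%. About 89% would lie beyond 7 months, with a median interval of about 15 months.

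**If 7 May 2018 is only the last mailing of a rolling schedule.** Earlier patients could have been mailed at six months and the wide range does not arise. What remains is the 35-day shortfall for the last patient. A mailing on 7 May 2018 is at six months only for a last visit on 7 November 2017.

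**The case against.** The strongest reply is that SAP 3.7 need not mean one mailing for everyone. The date follows directly on the last patient's visit and is followed by a reference to the protocol section that contains the six-month rule, so it may be the end of a rolling schedule. The sentence is also in the future tense in an SAP dated 29 May 2018 and created on 14 February 2018, so it records a plan rather than what was sent. This stands. A reader might infer that the follow-up values do come from 5 to 25 months after treatment; the documents do not establish that. The wording leans towards a single mailing, and on a rolling schedule anyone whose last visit fell before mid-August 2017 would already have been mailed when the SAP was created. That is inference, not proof.

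It also stands that the upper end rests on a planned start, that the six-month label is the protocol's and not the SAP's, and that the comparison between arms is not threatened. Randomisation in blocks of 4 or 8 (SAP 3.2) should keep the interval similar across arms. A reader might infer confounding, and nothing in the documents supports that. These outcomes are secondary, and Protocol 11.3.3 calls all such analyses explorative.

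Some remedies that come to mind are weak. Time to questionnaire return is undefined for non-responders, who are the patients 6.6.5 imputes, and the glossary lists no return date. A 5-to-7-month subset would hold about 10% of patients on the literal reading with even spread, some 15 of the planned 150. A main effect of time does not address a fading effect, which needs an interaction with briefing.

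The objection does not remove the conflict. Neither reading gives six months for the last patient, the SAP does not say which reading is meant, and the models take no account of the interval.

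**Conclusion.** The point holds as an unreconciled conflict with a conditional range. Certain from the documents: one stated mailing date, 147 days (4.8 months) after the last patient's visit and 35 days short of the protocol's six months, and follow-up models without an elapsed-time term. Conditional on that date applying to all patients: intervals up to about 24 to 25 months on the planned March 2016 start, or about 19 months on an assumed start of 1 September 2016. The share of about 10% at 5 to 7 months further assumes evenly spread treatment ends.

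The consequence is for interpretation and precision. Until the intervals are known, the follow-up results should not be reported as a six-month effect. The loss of precision cannot be sized, because the documents do not say how pain changes with elapsed time. Primary outcomes 1a, 1b and 2 are complete by session 8 and are untouched.

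**What to change.** 1. Reconcile SAP 3.7 with Protocol 9.3.8: state whether mailing was single or rolling, and record the mailing date for each patient. If earlier patients were mailed individually at six months, a corrected sentence settles most of the point.
2. Derive time from last session to mailing and report its distribution by arm. Session dates are already named in SAP 6.2.3, and this interval exists for non-responders. Protocol 8.4 intends no follow-up of withdrawn patients, so a rule is needed for anyone not mailed, such as the scheduled mailing date.
3. Add the interval as a covariate in 6.6.5, A.3 and A.4, in the extended follow-up pain model of 6.4.3, and in the follow-up imputation model. If the spread is wide, add an exploratory `EXPBRIEF`-by-interval term. With a single mailing date the interval and the calendar date of treatment carry the same information, so that term could not separate the two.
4. Describe the outcome as follow-up, with its actual range, unless the intervals turn out close to six months.

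The cost is one derived variable, one extra model term (two with the interaction), a few sentences in the SAP, and a less tidy label for the time point.

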## 4 Statistical Principles

### 4.1 Confidence Intervals and $p$ -Values

All confidence intervals are 95% and two-sided. All tests are two-sided and performed at a significance level of 0.05.

### 4.2 Adherence and Protocol Deviations

A few patients did not fill in the baseline questionnaire. Baseline values are, therefore, missing. A few patients stopped the acupuncture treatment prematurely and did not receive the foreseen eight acupuncture session. All patients received the briefing intervention as foreseen. Some patients used opioids between acupuncture sessions, which was initially an exclusion criteria at baseline if used on a regular basis.

### 4.3 Analysis Population

- For research question 1a, there are very few patients who did not fill in the baseline questionnaire. An intention-to-treat analysis will be performed using multiple imputation (cf. Section 6.5) to handle missing values.
- For research questions 1b, an intention-to-treat analysis will be performed using multiple imputation (cf. Section 6.5) to handle missing values.
- For research questions 2, an intention-to-treat analysis will be performed (no missing data handling needed, cf. Section 6.2.3).
- In a sensitivity analysis (cf. Section 6.4.1), per-protocol analyses will be done using a complete-case data set (research questions 1a and 1b). In addition, to assess the influence of protocol deviations (cf. 6.4.2), the analyses will be repeated without patients that used opioids (for research question 1b), and only with patients that had at least 6 out of the 8 acupuncture treatment sessions (for research question 1b), respectively.

## 5 Trial Population

### 5.1 Screening Data

See Study Protocol, Section 7.2, Recruitment and Screening, p. 26.

### 5.2 Eligibility

See Study Protocol, Section 7.1, Eligibility Criteria, pp. 25f.

### 5.3 Recruitment

See Study Protocol, Section 7.2, Recruitment and Screening, p. 26.

### 5.4 Withdrawal/Follow-up

See Study Protocol, Section 7.4, Criteria for Withdrawal/Discontinuation of Participants, p. 26.

### 5.5 Baseline Patient Characteristics

All variables used in the statistical analysis will be summarized. Continuous data will be summarized by mean, standard deviation (SD), minimum, maximum, 1st quartile, median, 3rd quartile, interquartile range, number of observations used, and number of observations missing. Categorical data will be summarized by numbers and percentages. This description will be done for the total sample and the four randomized groups respectively.

## 6 Analysis

### 6.1 Outcome Definitions

The three primary outcomes are

- 1a) Expectation of acupuncture treatment (questionnaire "P2 EAT", now called ETS, but will be labelled with EAT in this SAP), a score based on 5 questions having each 4 levels. It can range from 5 to 20. The questionnaire is filled in by the patients at baseline before the treatment (*i. e.* the briefing by the study doctor), immediately after the treatment, and once more after the 4th acupuncture session (in week 2).
- 1b) Average pain intensity over the last 7 days after 4 weeks at the end of the treatment (questionnaire "P7.2 NRS"). As a measure, a numeric rating scale (NRS) is used in a self-reporting fashion. The NRS has 11 discrete levels from 0 (no pain) to 10 (worst pain possible). The NRS is filled in at baseline (before the treatment), after two weeks, and at the end of the acupuncture sessions. Note that due to eligibility criteria, only patients with an NRS value  $\geq 4$  were included in the study. Accordingly, the baseline values of pain intensity lie within the range of 4–10.
- 2) The side effects score after each acupuncture session (questionnaire "P9 Nebenwirkungen"). A self-report questionnaire with 13 questions and 4 levels each (0 to 3) is used, thus the values range from 0 to 39 per session. As a secondary outcome, the total side effect score for each patient, adjusted for the number of acupuncture sessions that the patient actually received, will be used.

### 6.2 Analysis Methods

#### 6.2.1 Research Question 1a: The Expectation of Acupuncture Treatment (EAT)

The EAT score will be analyzed using analysis of covariance (ANCOVA). Outcome variable is the EAT score (EAT\_1b) obtained immediately after the effectiveness briefing (regular or high). Covariate of interest is the effectiveness briefing group (EXPBRIEF). As adjustment variables, EAT at baseline (EAT\_BL), and gender (pers\_1\_2) will be used.

Missing values will be imputed (see Section 6.5). As a sensitivity analysis, the same model will be fitted again, using only complete cases (see Section 6.4). The estimated mean difference of the two briefing groups with 95% confidence interval and  $p$ -value will be reported. The estimated effects of the adjusting variables will not be shown. In addition, adjusted means with 95% confidence intervals will be reported for each treatment group, where EAT at baseline will be fixed at its mean, and the two genders effects will be weighted with 0.5.

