### 6.2.2 Research Question 1b: Average Pain Intensity at the End of Treatment

If the result of the analysis of research question 1a indicates a significant effect of briefing on the expectations of acupuncture treatment, research question 1b will be analysed. The pain intensity will be analyzed using ANCOVA. Outcome variable is the pain intensity (`nrs_8_1`) measured at the end of the acupuncture treatment. Covariate of interest is the effectiveness briefing group (`EXPBRIEF`). As adjustment variables, pain intensity at first visit (`screening_1a_4a`), gender (`pers_1_2`), acupuncture therapist (`acupuncturist`), and baseline optimism (`LOT_BL_optim`) and pessimism (`LOT_BL_pessim`) will be used.

Missing values will be imputed (see Section 6.5). As a sensitivity analysis, the same model will be fitted again, using only complete cases (see Section 6.4). The estimated mean difference of the two briefing groups with 95% confidence interval and  $p$ -value will be reported. The estimated effects of the adjusting variables will not be shown. In addition, adjusted means with 95% confidence intervals will be reported for each treatment group, where all continuous adjustment variables will be fixed at their mean, and the effects of acupuncture therapist and gender will be given equal weights over the factor levels (thus 0.5 for gender and 0.33 for acupuncturist).

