### **Procedure:**

Independent of the briefing intervention all patients will receive the patient information leaflet about the study with common information about possible side effects as part of the informed consent procedure at the first visit. We transferred the basic safety profile from a study observing over 2 million acupuncture treatments into a patient information leaflet that is available for routine clinical care (Witt et al., 2009).

The briefing interventions will be provided through in-person contact with the doctor and also include written materials for the patients to take home before the first treatment session. The written materials have been adapted to the four groups. The initial effectiveness briefing will have a duration of about 20 minutes; the initial safety briefing will have a duration of 10 minutes. A manual for the briefing interventions has been developed and the medical doctors providing the briefing intervention will be trained in the briefing intervention as well as in communication skills (empathic style).

Patients will have a face-to-face booster visit according to their group allocation at the second treatment session, which will take around 15 minutes (10 minutes effectiveness briefing and 5 minutes safety briefing).

As a second booster, patients will receive emails or letters including a reminder of their appointments, more information about acupuncture for chronic low back pain as well as possible side effects according to their group allocation after the third and sixth acupuncture session.

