### **9.3.2 Baseline (Visit 1a)**

The first visit will take place at the Institute of Complementary and Integrative Medicine. The patient will be asked to hand in the informed consent for study phase 1 he had signed after the telephone interview and the baseline questionnaire to the study center. The study center will check them for completeness.

From the physician, the patient will receive the patient information for study phase 2 (B2) and will be asked to read it carefully.

Thereafter, the physician will inform the patient in detail about the study. The patient will have the opportunity to ask questions concerning the second phase of the study. The second informed consent will be given to the patient and he will be asked to read and sign it if he or she is still interested to participate in the study.

The physician will then check the inclusion criteria (See B1: demographic data, pain duration and severity ( $\geq 4$  NRS), health status and patients' medical history/comorbidity).

The appointments fixed at the first phone screening will be provided to the physician by the study center. The physician and the patient will go through all the appointments to confirm that the patient can come for acupuncture on all dates.

In case of inclusion, the physician will assign the patient to a group allocation via secuTrial.

Afterwards, the briefing will take place for around 30 minutes. In the course of this briefing, material will be provided to the patient to take home (see brochures).

In addition the physician will give the patient the EAT (P2) and CARE (P4) and ask him to complete them immediately and to hand out P2 and to put P4 into an envelope. The physician will meanwhile fill in the adherence questionnaire B4.

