### **9.3.4 Visit 2**

The second visit should take place within 2-7 days after the first acupuncture session. Before the second visit, participants will experience their booster session (according to the group allocation), which will take ca. 15 minutes (10 minutes effectiveness briefing and 5 minutes

safety briefing) and will be guided by the physician who also did the initial briefing session. The physician will again fill out the adherence questionnaire B5.

At the beginning of the acupuncture session, the side effects (P9) of the last acupuncture session will be measured and the weekly rescue medication diary (P6) will be checked. Patients will then receive the second acupuncture treatment.

After the session, the acupuncturist will fill out the adherence questionnaire A2.

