### **11.3.2 Primary Analysis**

The significance level will be set to  $\alpha = .05$ . It will be tested two-sided.

For the first hypotheses (1a) we will use an analysis of covariance (ANCOVA) with the fixed effects briefing group and sex and the covariate baseline expectation to determine the difference on expectation (EAT score) before the first acupuncture treatment between both briefing interventions.

For the second hypotheses (1b) to determine the difference in pain (numeric rating scale) after 4 weeks of acupuncture treatment we will use ANCOVA with the fixed effects briefing group, sex, therapist and the covariates baseline pain and optimism.

We use this hierarchical test procedure to control for multiple testing. In a first step, we will test if the briefing changes the expectation. Only if the null hypothesis 1a was rejected (high expectation briefing  $\neq$  regular expectation briefing) we will test in a second step whether the briefing changes pain after treatment (hypotheses 1b), using the same alpha level.

Sensitivity analyses for both analyses will include a.) adding various covariates to the model (e.g. age, duration of disease, depression, empathy), b.) changing the study populations (per-protocol), and c.) using different multiple imputation methods for missing data (hot deck and regression methods). Confidence intervals and p-values from sensitivity analyses are

considered explorative. The research question if briefing effects on pain are mediated by initial treatment expectations will be tested according to the framework suggested by Baron and Kenny (Baron & Kenny, 1986; Hayes, 2009) in a hierarchical regression analysis.

Research question 2: As primary analysis, the total side effect score after 8 sessions will be compared between safety briefing groups using zero-inflated and hurdle models for count data. This analysis will require to appropriately imputing intermittent missing side effect scores and dropouts. Alternatively, a longitudinal analysis of the side effect scores, available from up to 8 sessions, will be achieved through an appropriate model extension using patient-specific random effects. As no standard software is available for this, problem-specific implementation using Markov Chain Monte Carlo (MCMC) or INLA ([www.r-inla.org](http://www.r-inla.org)) will be used. Analyses will be conducted after LPLV by the statistician, presumably in the third year of the project.

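### The model for question 1a leaves out the briefing doctor; if several doctors briefed, adding the doctor is a cheap gain in precision for the test that opens the gate to 1b

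*Combined protocol and SAP*

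**What the plan says.** For 1a, SAP 6.2.1 compares the expectation score (EAT) after the briefing between effectiveness groups by ANCOVA. The covariates start with "As adjustment variables, EAT at baseline" and end with gender. Protocol 11.3.2 agrees: "fixed effects briefing group and sex and the covariate baseline expectation".

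For 1b, SAP 6.2.2 adds a provider term, "acupuncture therapist (`acupuncturist`), and baseline optimism", as does protocol 11.3.2: "fixed effects briefing group, sex, therapist and the covariates baseline pain and optimism". SAP 6.2.2 treats the acupuncturist as a factor: "the effects of acupuncture therapist and gender will be given equal weights over the factor levels".

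No briefing-doctor term appears in the question 2 model (SAP 6.2.3), the extended models (6.4.3), the factorial analyses (6.6.4), the PSM models (6.6.6) or Appendix A. None appears in the imputation lists (6.5, 6.6.5) or the glossary (Appendix B).

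The briefing is given by a doctor who takes no part in the acupuncture (protocol 6.2.2). The Procedure part of protocol 8.1 uses the plural: "the medical doctors providing the briefing intervention will be trained in the briefing intervention as well as in communication skills (empathic style". The booster at visit 2 "will be guided by the physician who also did the initial briefing session". After the first briefing, while the patient completes the EAT, "The physician will meanwhile fill in the adherence questionnaire B4" (protocol 9.3.2). Randomisation is stratified by sex only (SAP 3.2, protocol 6.2.1), and 1b is tested only if 1a is rejected (SAP 3.4).

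**The concern.** The SAP accepts in 1b that the provider can matter, but its adjustment is for the provider of the treatment common to all arms. The person who delivers the randomised intervention is in no model. Provider differences are plausible for the EAT in 1a: the same doctor gives the talk and hands over the questionnaire minutes later.

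Doctor is not a stratification factor, so any difference between doctors that is common to both arms stays in the residual of the 1a comparison. That comparison is also the gate: if 1a is missed, the pain question, planned at only 56–65% power (SAP 3.3.2), is not tested at all. At stake is therefore some power at the gate, together with the reader's ability to see whether the briefing effect was similar across the people who gave it.

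**Working it through.** **Inputs from the documents.** SMD 0.5, two-sided 5%, 80% power, 64 per effectiveness group, 150 to be enrolled (SAP 3.3.1). I take the SMD to be in units of the SD that the present model leaves, since the plan makes no allowance for covariates.

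**Inputs not in the documents.** The number of briefing doctors, and the share R² of residual EAT variance that lies between them. I use R² of 2%, 5% and 10%.

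**The plan's own figure.** Noncentrality 0.5/√(1/64 + 1/64) = 2.83 on 126 degrees of freedom gives 80.1% power, so the 128 patients reproduce. The EAT is taken at the first visit, before later dropout can matter, so 75 per group may be nearer the truth; power there is 86.0%.

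**Adding the doctor.** With doctor crossed with arm, the residual SD shrinks by √(1 − R²). The standard error falls by 1 − √(1 − R²), and the detectable SMD becomes 0.5/√(1 − R²) = 0.505, 0.513 and 0.527.

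| R² (assumed) | SE reduction | Power, 64 per group (80.1% without doctor) | Power, 75 per group (86.0% without doctor) |
|---|---|---|---|
| 2% | 1.0% | 80.9% | 86.7% |
| 5% | 2.5% | 82.1% | 87.7% |
| 10% | 5.1% | 84.1% | 89.4% |

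In patients, 150 × R²/(1 − R²) gives about 3, 8 and 17. The degrees of freedom lost with 2 to 6 doctors change power by about 0.1 point or less.

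**What this formula leaves out.** It treats doctors as balanced over the arms. Since randomisation is not stratified by doctor, chance imbalance costs the adjusted analysis on average (J − 1)/(N − 1) of its information with J doctors. For N = 128 that is 1/127 = 0.8% with two doctors and 3/127 = 2.4% with four. At R² = 2% the net gain is therefore small with two doctors and about nil with four; at 5% and 10% a gain remains.

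**Simulation.** 6,000 trials per setting, 64 per arm, 2 or 4 doctors, doctor effects drawn at random with intraclass correlation 0.01, 0.05 or 0.10.
- Type I error was 4.9–5.5% without the doctor and 4.9–5.5% with it.
- At 0.10, power went from 82.2% to 83.8% (two doctors) and from 80.9% to 82.4% (four).
- At 0.01 there was no visible gain.

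The Monte Carlo standard error is √(0.8 × 0.2/6000) = 0.5 points. The simulated gains are smaller than the table's partly because of the imbalance cost. In addition, with few doctors the realised share is on average only (1 − 1/J) of the intraclass correlation, for example 5% rather than 10% with two doctors.

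**If the briefing effect itself varies between doctors.** Let its SD across doctors be τ, in outcome SDs, with k doctors. The standard error for a claim about doctors in general, relative to the reported one, is √[(4/150 + τ²/k)/(4/150)].
- τ = 0.2: 1.32, 1.22 and 1.17 for k = 2, 3 and 4.
- τ = 0.1: 1.09, 1.06 and 1.05.

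A main effect for doctor does not change this. In simulation with three doctors and an interaction variance of 0.02 or 0.05, false-positive rates for such a general claim were 7.7% and 12.5% without the main effect, and 7.8% and 12.9% with it.

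**The case against.** The strongest objection is that the premise may fail. Protocol 8.1 has the plural, but protocol 6.2.2 and 9.3.2 refer to the doctor in the singular. So does SAP 6.1, in a document dated after the last patient visit. Neither usage settles the number. If one doctor gave every briefing, the precision argument disappears. This stands, and the recommendation is conditional for that reason.

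Second, this is an optional covariate, not an error. Patients are individually randomised, any omitted prognostic variable leaves noise, and the confidence interval already reflects it. This also stands. A reader might infer that the omission biases 1a or inflates its error rate; the simulation shows that it does not for the trial's own doctors.

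Third, adjusting 1b for the acupuncturist is coherent in itself: that provider gives the sessions preceding the pain outcome, and the protocol prespecified the term. So the contrast is no inconsistency in 1b, only a sign that provider effects were considered for one provider and not for the other.

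Fourth, the extended models contain the CARE score, a rating of the briefing physician's empathy, and briefings follow a manual with adherence recorded. CARE is only a partial answer. It is completed after the briefing (protocol 9.3.2), may itself respond to the arm, and is absent from the primary models. The doctor's identity should not depend on the arm, because the including doctor randomises (protocol 7.3) and the briefing follows at the same visit. That each doctor delivers all arms is an inference from these sections, not a statement in them.

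**Conclusion.** The point holds as a modest improvement to 1a. Omitting the briefing doctor costs 1.0%, 2.5% or 5.1% of the standard error, and about 1, 2 or 4 points of power at 64 per group, if doctors explain 2%, 5% or 10% of residual EAT variance. The chance-imbalance cost makes the net gain somewhat smaller. All of this assumes more than one briefing doctor and rests on variance shares that the documents do not give.

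Three stronger readings are tempting and not supported:
- That the reported standard error is 17–32% too small. That range belongs to a different target (doctors in general), assumes τ = 0.2, and falls to 5–9% at τ = 0.1. Adding the doctor as a main effect would not alter it.
- That a positive 1a result could merely reflect one persuasive doctor. A doctor who is persuasive in both arms cancels in the contrast; only a briefing effect that differs between doctors raises this question, and a display by doctor addresses it.
- That the primary models for 1b and question 2 must change. No calculation supports this for the zero-inflated mixed model of question 2, and for 1b a sensitivity analysis is enough.

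**What to change.** State in the SAP how many doctors gave the briefings.

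If more than one:
- Add the doctor as a fixed factor to the 1a model in SAP 6.2.1, to the 1a imputation list in 6.5 and to the glossary, pooling doctors with few patients by a rule set in advance. Do this as a dated SAP revision while the statisticians are still blind to allocation.
- Add the doctor to 1b and question 2 as a sensitivity analysis only.
- Report the 1a briefing effect by doctor, descriptively and without a test.

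If there was one doctor, say so and limit the conclusion to a briefing by that provider.

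The cost is one degree of freedom per additional doctor, the small imbalance cost shown above, and a minor departure from the covariate list in protocol 11.3.2, to be recorded as such. The variable probably exists: the physician completes B4 and B5 for each patient, and protocol 13.1.1 requires that people making CRF entries can be identified. The forms themselves are not shown, so this should be confirmed first. If the departure from the protocol is unwelcome, keep the present 1a model as primary and report the doctor-adjusted version beside it. That gives up the power gain but keeps the information.
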